# TIMELAPSE study—efficacy of low-dose amitriptyline versus cognitive behavioral therapy for chronic insomnia in patients with medical comorbidity: study protocol of a randomized controlled multicenter non-inferiority trial

**DOI:** 10.1186/s13063-021-05868-4

**Published:** 2021-12-11

**Keywords:** Insomnia, Medical comorbidity, Amitriptyline, Cognitive behavioral therapy, CBT-I, Fatigue, Pain, Treatment preference, Non-inferiority

## Abstract

**Background:**

Insomnia is common in people with long-term medical conditions and is related to increased mortality and morbidity. Cognitive behavioral therapy for insomnia (CBT-I) is first choice treatment and effective for people with insomnia and comorbid long-term medical conditions. However, CBT-I has some limitations as it might not always be available or appeal to patients with medical conditions. Furthermore, a small proportion of patients do not respond to CBT-I. Preliminary evidence and clinical experience suggest that low-dose amitriptyline (AM) might be an effective alternative to treat insomnia in patients with medical comorbidity. In this randomized controlled trial, we will determine whether AM is non-inferior to the first choice treatment for insomnia, CBT-I.

**Methods/design:**

This study will test if treatment with low-dose amitriptyline for insomnia in patients with medical comorbidity is non-inferior to CBT-I in a multicenter randomized controlled non-inferiority trial. Participants will be 190 adults with a long-term medical condition and insomnia. Participants will be randomly allocated to one of two intervention arms: 12 weeks AM (starting with 10 mg per day, and if ineffective at 3 weeks, doubling this dose) or 12 weeks of CBT-I consisting of 6 weekly sessions and a follow-up session 6 weeks later. The primary outcome is subjective insomnia severity, measured with the Insomnia Severity Index (ISI). The primary endpoint is at 12 weeks. Secondary outcomes include sleep quality (e.g., sleep efficiency), questionnaires on daytime functioning (physical functioning and impairment of functioning), and symptoms (e.g., fatigue, pain, anxiety) at 12 weeks and 12 months post treatment and relapse of insomnia until 12 months after treatment.

**Discussion:**

Irrespective of the outcome, this study will be a much-needed contribution to evidence based clinical guidelines on the treatment of insomnia in patients with medical comorbidity.

**Trial registration:**

Dutch Trial Register NTR NL7971. Registered on 18 August 2019

**Supplementary Information:**

The online version contains supplementary material available at 10.1186/s13063-021-05868-4.

## Background

Insomnia disorder is prevalent (up to 66%) in patients with long-term medical conditions [1, 2]. Patients with a medical condition are 2.2 times more likely to have insomnia than patients without medical problems [3]. In DSM-5, insomnia disorder is defined as the complaint of poor sleep occurring at least 3 nights per week for at least 3 months with associated significant daytime effects [4]. Insomnia has been associated with an increased risk of various medical [5–7] and psychiatric disorders [8, 9] and injuries [10]. Sleep disorders in patients with medical conditions are assumed to negatively affect prognosis [11]. In patients with chronic illness, insomnia is independently associated with a significant decrease in overall quality of life [12]. The economic burden of insomnia in general is reported to be high. Health care use is reported to be twice as high among people with insomnia compared to those without, and insomnia-related work absence and reduced productivity are the main drivers of societal costs [13, 14]. Therefore, treatment of insomnia in patients with medical comorbidity is of utmost importance for health and functioning.

Insomnia treatments can be broadly divided into pharmacological (mainly benzodiazepine receptor agonists) and non-pharmacological. The European guideline for the diagnosis and treatment of insomnia recommends non-pharmacological treatment as first choice, of which cognitive behavioral therapy (CBT-I) is the most important one [15].

CBT-I is a multicomponent treatment package, applied face to face or online [15]. It includes behavioral and cognitive components, such as sleep hygiene education, stimulus control and sleep restriction interventions, relaxation techniques, and cognitive therapy. CBT-I has been found to improve sleep in about 70–80% of the participants both in individual and group treatment [16–19] and sustained effects were found on sleep and depression parameters [20]. A variety of studies have assessed the efficacy of CBT-I for insomnia comorbid with psychiatric and medical illness. Remarkably, the pre to post-treatment effect sizes in patients with comorbidities are comparable with those for primary insomnia and in some cases larger [21]. Furthermore, there is growing evidence that improved sleep following CBT-I positively influences the clinical course of the comorbid condition [22, 23].

In the short term, benzodiazepine receptor agonists (BZRAs) are as efficacious as CBT-I. In the long term, there is more support for efficacy of CBT-I in comparison to BZRA’s [24], given the higher relapse rates in BZRA’s when active treatment is discontinued. Therefore, the European guideline for the diagnosis and treatment of insomnia advises the use of BZRA’s only in short-term if CBT-I is ineffective or unavailable, in order to avoid their serious disadvantages, i.e., the rapid development of tolerance, dependence, adverse side effects and rebound effects [15]. Preventing adverse side effects (e.g., fall risk) is particularly relevant for patients with long-term medical conditions.

Despite this guideline, in the Netherlands BZRA’s are still often prescribed [25]. Several studies describe that clinicians often assume that patients with chronic insomnia prefer pharmacological treatment above psychological treatment [26–30]. Furthermore, CBT-I has several limitations. First, not all insomnia patients can access CBT-I, since CBT-I is still not widely implemented [28, 31] and conducting CBT-I in patients with medical comorbidity requires specialized practitioners [31, 32]. Second, not all insomnia patients are willing to undergo CBT-I. Stimulus control and sleep restriction are important components of CBT-I which mediate the reduction of insomnia, but initially, these components result in sleep deprivation and an increase of daytime sleepiness. The delayed therapeutic effect requires substantial motivation and effort. Patients with insomnia often perceive sleep restriction as unappealing and difficult to implement [33]. Adherence to stimulus control and sleep restriction has found to be relatively low, which negatively impacts outcome. In particular, patients with medical comorbidity can experience these components as strenuous or might be unable to fully engage in CBT-I due to their medical condition with associated disease burden. Third, there remains a proportion of individuals in which insomnia does not respond to (approximately 20%) or remits (40%) after CBT-I treatment [20]. Therefore, in addition to CBT-I as treatment for chronic insomnia, there is a need for effective, safe, and less strenuous alternatives for CBT-I that are suitable for patients with insomnia and long-term medical conditions.

In primary and secondary care settings in the Netherlands, several drugs are used off-label to treat insomnia [34], among which is amitriptyline in low dosage (AM) [35]. AM is a generic antidepressant commonly used in treatment of major depression. In low dosages, AM is also indicated for the treatment of neuropathic pain. Research to explore hypnotic efficacy in insomnia has not been done before [36], but clinical experience indicates that amitriptyline is effective in treating insomnia. Romenets e.a [37]. compared CBT-I with 6 weeks doxepin (a sedating tricyclic antidepressant as well) 10 mg at bedtime in patients with Parkinson’s disease and comorbid insomnia and found comparable effects.

Off-label prescription in general increases the risk of unnecessarily exposing patients to drugs without knowing how effective they are [38], which is undesirable, especially in a relatively fragile population with medical conditions. A head-to-head comparison of the current off-label use of AM as sleep medication and CBT-I is needed in patients with chronic insomnia and medical comorbidity. The randomized controlled non-inferiority TIMELAPSE trial will compare the use of low-dose AM with first choice of treatment (CBT-I) and determine if AM is non-inferior to CBT-I. Additionally, we want to explore mediators of the two treatments to improve knowledge of the working mechanisms leading to therapeutic change. Evidence suggests that CBT-I leads to changes in the cognitive, behavioral, and hyperarousal precipitating factors of insomnia (pre sleep arousal and dysfunctional attitudes and beliefs about sleep) [39]. Unclear is how AM will affect these elements. Finally, we wish to explore moderators of the treatment response, i.e., treatment preference, causal attributions of insomnia and insomnia subtypes [40].

## Objectives

### Primary objective

Our primary objective is to assess whether a 12-week treatment period of low-dose AM (10–20 mg nightly) is non-inferior with respect to its effect on insomnia severity compared to CBT-I in insomnia patients with long-term medical conditions.

### Secondary objective

Secondary objectives include to evaluate 1) relapse in insomnia rates in both groups up to 12 months post treatment, 2) secondary outcomes after 12 weeks and 12 months of treatment (sleep quality, fatigue, pain, depression, anxiety, physical functioning, impairment of functioning), 3) treatment evaluation (side-effects, adherence and withdrawal), and 4) possible mediators and moderators of treatment outcome.

## Methods/design

This study is a multicenter randomized controlled non-inferiority trial in which treatment with low-dose (10–20 mg nightly) AM is compared with the golden standard, CBT-I. Eligible consenting patients are randomized to 1) CBT-I or 2) low dose of AM, both for a period of 12 weeks in a ratio of 1:1. Patients are followed up to 12 months post treatment (thus 15 months post randomization). The study is implemented in regular care of the outpatient clinic of the departments of neurology (sleep-wake center) and departments of medical psychology of the participating Dutch hospitals (see Fig. 1 for a flow chart).

**Fig. 1 Fig1:**
[figure not shown]
Trial flow chart

### Participants

Patients known with a long-term medical condition, aged 18–85 years old, suffering from insomnia disorder meeting DSM-5 criteria, and scoring ≥ 10 on the Insomnia Severity Index (ISI) [41] are eligible for participation [42]. A long-term chronic medical condition refers to all long-term medical conditions and/or persistent physical complaints (> 3 months) that require medical attention (in the form of consultation in medical health care, medication, aid or treatment) that cause dysfunction, discomfort, or social problems. The upper age limit is conform the guideline for low-dose amitriptyline treatment of neuropathic pain and the Food and Drug Administration approved use of doxepin (a sedating tricyclic antidepressant as well) in the treatment of insomnia. The DSM-5 criteria for insomnia disorder are sleep problems in at least 3 nights a week, for at least 3 months with consequences for daytime functioning, and the sleep problem cannot be better explained by or occurs exclusively during the course of another sleep disorder.

### Exclusion criteria

The study-related exclusion criteria are 1) habitual night shift worker, 2) an untreated sleep-related breathing disorder, 3) a wish to continue over-the-counter sleep aids as melatonin and medicinal cannabis, 4) the use of off-label amitriptyline for insomnia in the past year, 5) being unable to follow study instructions and fill out the study questionnaires in Dutch, 6) a known diagnosis of dementia or history of delirium and epilepsy, 7) pregnancy, lactation, or wish to become pregnant in the coming 6 months, 8) the presence of a severe psychiatric disorder (not in remission or not adequately treated), 9) current alcohol or drug abuse/addiction (benzodiazepine excluded), 10) terminal illness (life expectancy less than one year), 11) ocular hypertension/glaucoma, and 11) participation in other interventional studies. Furthermore, to prevent potential drug to drug interaction, subjects with 13) a current use of psychopharmaceuticals other than benzodiazepine such as antidepressants (selective serotonin reuptake inhibitors , tricyclic antidepressants, MAO-inhibitors), St John’s worth, anticonvulsants (e.g., carbamazepine), and antimyotics are excluded. Finally, subjects who are known with 14) any of the following contra-indications for amitriptyline conform pharmacological guidelines as used in clinical practice will be excluded: an allergy for amitriptyline, cardiovascular diseases (cardiac arrhythmia/blockade/long QT syndrome/Brugada syndrome, family history of acute cardiac death, recent myocardial infarction (within the past 90 days), and angina pectoris/coronary insufficiency), severe renal insufficiency (GFR < 10) or severe liver dysfunction. The exclusion criteria are based on guidelines of higher dosage amitriptyline. They are lined up to prevent, e.g., the risk of cardiac dysrhythmias, withdrawal symptoms in the newborn, and suicidal risk. Patients with dementia, severe psychiatric disorders (including suicidal risk), and patients who are not able to follow study instructions are excluded for the study, to prevent the risk of overdoses.

Table 1 summarizes the inclusion and exclusion criteria.

**Table 1 Tab1:** Inclusion and exclusion criteria

Inclusion criteria	Exclusion criteria
18–85 years Insomnia disorder conform DSM-5 Score of ≥ 10 on the Insomnia Severity Index Long term medical condition	*Study-related exclusion criteria:* Habitual night shifts Untreated sleep-related breathing disorder Wish to continue over-the-counter sleep aids Off-label amitriptyline for insomnia in past year Epilepsy, dementia, history of delirium Pregnancy, lactation or pregnancy wish Terminal illness Ocular hypertension/glaucoma Severe psychiatric disorder Substance abuse/addiction (benzodiazepine excluded)
	*Potential drug-drug interactions for amitriptyline:* Use of psychopharmaceuticals (other than benzodiazepine) or antimyotics
	*Contra-indications for amitriptyline:* Allergy for amitriptyline Cardiac disorders Severe renal insufficiency or liver dysfunction

### Recruitment

Patients treated in medical health care (e.g., hospital, rehabilitation clinic, general practice) for their medical problems will be approached; treating physicians, nurse specialists, or nurse practitioners will inform patients who have complaints of insomnia with verbal and written information about the study during regular medical follow-up consults. Patients will also be informed about the study by leaflets and notifications on social media, narrow casting in the participating general hospitals, newsletters, and websites of patient associations.

If a patient is interested in the study, the general practitioner or medical specialist refers to the multidisciplinary diagnostic procedure for patients with long-term medical conditions and complaints of insomnia of the three participating general hospitals. In case patients are informed outside the care provision (e.g., by social media) and wants to participate (self-referral), a referral by a physician is required as well.

### Procedures

The multidisciplinary inclusion procedure consists of a consultation with a psychologist and a neurologist. During these appointments, criteria for insomnia (conform the DSM-5), (co)existence of other sleep wake disorders and possible exclusion criteria for treatment options are checked based on the referral information of the medical specialist or general practitioner (e.g., nature, severity and treatment of medical or psychiatric problem), medical history, clinical interview (e.g., medication use), and if necessary polysomnography (e.g., in case of complaints typically for sleep-related breathing disorder).

When a patient is considered eligible for the present study, the specialists involved in the procedure give brief information (orally) about the study, answer questions, and hand out the written patient information sheet and informed consent. Eligible patients will be informed (in a face-to-face contact or by phone) with a research assistant who answers questions, obtains the informed consent, and explains the study procedure.

Upon written consent, the baseline questionnaires and baseline sleep diary with instructions are provided online and the researcher or research assistant documents any over the counter medication. Finally, a double check on pharmacological eligibility is done by pharmacy of the participating hospital.

### Randomization and blinding

When the baseline questionnaires and the sleep diary are completed, the participants are randomized. Randomization is computer generated, by the webbased system (CastorEdc). Block randomization (blocks of 2 or 4) will be used to create similar distributions in the different study arms. Randomization into the two treatment groups is at patient level and will be stratified by benzodiazepine use, at least once every 2 weeks (i.e., no *versus* benzodiazepine use) at baseline and by referral type (self-referral versus referral by health care worker). Randomization will be executed centrally by a researcher/assistant who is not involved in the recruitment and inclusion of patients.

The research assistant informs the participants by phone about the result of the randomization procedure and explains the CBT-I appointment or how to collect the medication at the hospital pharmacy. The coordinating researcher and participant agree upon and document the date on which the participant will start taking/attending the study treatment.

It is not possible to blind participants or therapists to allocation; statistical analysis will be conducted by an independent statistician who will be blinded for group allocation.

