## Trial status

Recruitment is ongoing. Recruitment began in September 2019 in Hospital Gelderse Vallei, Ede, the Netherlands. From November 2020, recruitment started in Hospital Zaans Medical Centre, Zaandam, and Hospital Rivierenland, Tiel, and from June 2021 in Hospital Jeroen Bosch, ‘s-Hertogenbosch, all in the Netherlands as well. At the time of submitting the protocol, 75 of 190 participants (39%) have been consented and 68 randomized. Current protocol version 4.3 is dated August 2020.

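### Published blocks of 2 or 4 in an open-label trial still recruiting make upcoming allocations partly predictable to anyone who follows earlier allocations in a stratum

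*Protocol article*

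**What the plan says.** Under Randomization and blinding, the protocol article fixes the block sizes: "Block randomization (blocks of 2 or 4) will be used to create similar distributions in the different study arms". Allocation is "both for a period of 12 weeks in a ratio of 1:1" (Methods/design). The same section adds: "Randomization into the two treatment groups is at patient level and will be stratified by benzodiazepine use", with referral type (self-referral or not) as the second factor. Two factors with two levels each make four strata, and hospital is not a listed factor. It also states: "It is not possible to blind participants or therapists to allocation".

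The safeguards are in that section too. Randomisation is computer-generated, executed centrally by a person with no part in recruitment or inclusion, and done only after the baseline questionnaires and sleep diary are complete.

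On roles, Procedures has eligible patients speak with "a research assistant who answers questions, obtains the informed consent, and explains the study procedure". Randomization and blinding then says: "The research assistant informs the participants by phone about the result of the randomization procedure". A neurologist and a psychologist conduct the inclusion consultations (Procedures). The same two professions see amitriptyline patients during treatment and deliver CBT-I (Interventions).

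Trial status says: "Recruitment is ongoing". At submission 68 of 190 had been randomised.

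**The concern.** Concealment needs two things: the list must be hidden, and the next entry must not be deducible from earlier ones. Central execution secures the first. The second is weak when allocations are open, blocks are very small and their sizes are public. The roles that screen and consent patients also have tasks that reveal earlier allocations.

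If recruiters can guess the next arm better than chance, they can change how strongly they encourage a patient, or when. The arms may then differ in motivation or expectation. The primary outcome, the ISI, is self-reported and participants are unblinded. Adjusting for baseline ISI removes only the part of such a difference that baseline ISI explains. In a non-inferiority trial, a shift in favour of amitriptyline could support a false claim.

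**Working it through.** The protocol gives no predictability figure, so there is none to reproduce.

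**Inputs from the article:** block sizes 2 and 4, ratio 1:1, four strata.

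**Assumptions:** each block has size 2 with probability p = 0.5 (range 0.25 to 0.75). A stratum holds about 48 patients (190/4 = 47.5). The observer knows the two possible sizes but not the size of any given block.

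**Step 1, a single fixed size.** Guess the arm that is behind, and toss a coin when the arms are level.
- Block of 2: expected correct = 0.5 + 1 = 1.5 of 2, or 75%. One of two is certain (50%).
- Block of 4: expected correct = 0.5 + 2/3 + 2/3 + 1 = 2.83 of 4, or 71%. Certain = (1/3 + 1)/4 = 33%.

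**Step 2, sizes 2 and 4 mixed, every earlier allocation in the stratum seen.**
- Mean block length = 2p + 4(1−p) = 3 at p = 0.5.
- Correct = [1.5p + 2.83(1−p)]/3 = (0.75 + 1.417)/3 = 72%. At p = 0.25 it is 2.50/3.5 = 71%, and at p = 0.75 it is 1.83/2.5 = 73%.
- Certainty arises only when a block of 4 opens with the same arm twice (probability 1/3), which fixes the last two places. Certain = (1−p)(1/3)(2)/3 = 1/9, or 11%. At p = 0.25 it is 0.5/3.5 = 14%, and at p = 0.75 it is 0.167/2.5 = 7%.
- Simulation of a Bayes-optimal observer (4,000 sequences of 48) gives 72.1% correct and 10.7% certain.

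**Step 3, patients randomised between the guess and the allocation.** Randomisation follows the questionnaires and a one-week diary, so others in the stratum may go first. Simulated results for an observer who knows the sizes:

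| Intervening patients | 2/4: correct | 2/4: certain | 4/6/8: correct | 4/6/8: certain |
|---|---|---|---|---|
| 0 | 72% | 11% | 68% | 2% |
| 1 | 55% | 5% | 60% | 1.5% |
| 2 | 53% | 0% | 57% | under 1% |
| 3 | 50% | 0% | 53% | under 1% |

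**Step 4, partial sight of a stratum, nobody intervening, sizes 2/4.**

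| Share of allocations seen | Knows when the unseen ones occurred | Unaware of the unseen ones |
|---|---|---|
| 75% | 66% | 58% |
| 50% | 61% | 55% |
| 25% | 56% | 53% |

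The last column fits someone who sees only one hospital.

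**Step 5, scale of possible bias (illustration).** Suppose patients enrolled when amitriptyline is guessed differ by d ISI points from those enrolled when CBT-I is guessed, and every enrolment follows the guess. The arms then differ by (2 × proportion correct − 1) × d. With d = 1, an assumed value, that is 0.44 points at 72% and 0.10 at 55%, against a margin of 4.

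**The case against.** The strongest reply is that the safeguards are real and the 72% needs conditions that may rarely hold. The person running randomisation is outside recruitment. Hospital is not a stratum, so each stratum's sequence runs across sites, and Trial status names four hospitals. The delay between consent and randomisation means that one intervening patient cuts the guess from 72% to about 55%. At submission 75 had consented and 68 were randomised, so up to seven may have been waiting, although some may have dropped out. All of this stands and limits the size of the problem.

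It also limits the remedy. With one or two patients intervening, blocks of 4, 6 and 8 are on average slightly more guessable than blocks of 2 and 4 if the observer knows the sizes. That stands too.

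Three stronger readings are tempting but unsupported:
- **That staff who obtain consent know the allocations.** The same job title appears in both tasks, but the article does not say it is one person. The assistant who phones the result could be the uninvolved one, and nothing says that one assistant covers all hospitals.
- **That strong preferences among participants aggravate the risk.** The Discussion says patients with strong preferences may be less willing to join, and commits to measuring preference.
- **That 122 patients were unprotected once the sizes were public.** The difference 190 − 68 = 122 dates from submission. The number outstanding at publication is not given.

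The reply does not dispose of the point. Hiding the list does not prevent deduction. Anyone who follows allocations across hospitals, as a coordinating researcher who agrees start dates with participants might, comes closer to the ceiling than staff at one site.

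**Conclusion.** The point holds as a minor weakness in allocation concealment. Upcoming allocations are partly predictable, not generally known. The ceiling is 72% correct (71–73% over the assumed size mixes) and about 11% certain (7–14%). It requires full sight of a stratum, knowledge of the sizes and nobody intervening. More ordinary conditions give about 53–58%, close to chance.

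These figures assume the two sizes are mixed at random, which the article does not state. A single fixed size would be worse for certainty (50% or 33%). The article does not establish who actually sees what, and nothing in it shows that selection has taken place.

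**What to change.** For patients still to be randomised, drop blocks of 2, use larger sizes varied at random (for example 4, 6 and 8), and keep the new sizes out of any document open to recruiting staff until recruitment ends. Completing the open block in each stratum before switching avoids adding imbalance.

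The gain is mainly in certain allocations: about 11% to 2% with nobody intervening, and 5% to 1.5% with one. Average guessability falls only from 72% to 68% in the first case and does not improve in the second for an observer who learns the new sizes, so non-disclosure is an essential part of the change. How much non-disclosure adds was not calculated, and guessing the arm that is behind needs no knowledge of the sizes.

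The cost is a setting in the randomisation system and an amendment line. The largest possible within-stratum imbalance rises from 2 to 4, so the extreme over four strata rises from 4 × 2 = 8 to 4 × 4 = 16 of 190 patients. The primary analysis need not change.
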